### Concealment mechanism {16b}

The research team will receive information regarding the assignment of participants to the different intervention groups by means of sealed opaque envelopes

### Implementation {16c}

Randomization and allocation concealment will be conducted by independent researchers.

## Assignment of interventions: Blinding

### Who will be blinded {17a}

Participants will receive basic information about the study but not about the study objectives or which intervention is considered active. The psychotherapists involved in conducting the interventions will not receive detailed information about the study objectives. The members of the research team involved in assessing the participants will not receive information about the study objectives, the group assignment, or the results expected to be obtained in the study. In addition, the data analyst will be blinded to the allocation of participants to the different study groups.

## Procedure for unblinding if needed {17b}

Not applicable. Unblinding will not be carried out until the study is completed.

## Data collection and management

### Plans for assessment and collection of outcomes {18a}

#### Mini-Mental State Examination (MMSE)

The MMSE consists of a quantitative screening test of cognitive function comprising 11 questions that are administered between 5 and 10 min. Three items are scored from 0 to 5, 3 items are scored from 0 to 3, 1 item is scored from 0 to 2 and 4 items are scored from 0 to 1. The maximum score that can be obtained is 30, with a higher score indicating less cognitive impairment. A score below 24 points indicates possible cognitive impairment. The validity of MMSE has been demonstrated in a Spanish population with a Cronbach’s alpha of .94 [27, 28].

#### Functional Assessment of Cancer Therapy-Cognitive Function, version 3 (FACT-Cog)

This instrument was developed to assess chemotherapy-induced cognitive problems in cancer patients. This 37 items scale includes four different subscales: Perceived Cognitive Impairments, Impact of Perceived Cognitive Impairments on QoL, Comments from Others, and Perceived Cognitive Abilities. The sub-scales are scored using a 5-point Likert scale from 0 (*never*) to 4 (*several times a day*). Some items are reversed score. Higher scores reflect fewer cognitive problems and better QoL. This instrument has good psychometric properties with α = .94 [29, 30].

#### Memory Failures Everyday (MFE-30)

The MFE-30 is a unifactorial questionnaire that measures a single construct: “cognitive complaints.” It is made up of 30 items that are answered on a 5-point Likert scale from 1 (*never*) to 4 (*always or almost always*). The minimum score is 30 and the maximum score is 120, with higher scores indicating poorer memory function. The test has been validated in the general Spanish population with Cronbach’s alpha scores between .91 and .93 [31].

#### Hopkins Verbal Learning Test-Revised (HVLT-R)

This test measures primary and secondary memory, the rate of verbal learning throughout three trials, as well as three forms of mnesic organization: serial ordering, semantic grouping, and subjective organization. The test consists of a list of 12 words that are presented orally at a speed of one word for every 2 s. The person tested scores 1 point for every word remembered. The maximum total score after the three trials is 36 and the minimum score is 0. The more words remembered, the better the memory functioning. According to the International Cognition and Cancer Task Force (ICCTF) [32], the HVLT-R is one of the essential, recommended tests and has good internal consistency with *α* = .81 [33].

#### Trail Making Test (TMT)

The TMT consists of two parts: Part A measures attention, processing speed, visual search, and working memory, while Part B is used to measure attention, executive function (cognitive flexibility, ability to change tasks, coordination of categories), working memory, visual-motor skills, and processing speed. It uses time as a measure of cognitive performance. The less time it takes, the better the cognitive processing. Scores higher than 78 seconds on Part A and 273 seconds on Part B are considered deficient. The test shows good internal consistency (*α* = .83) [34]. Furthermore, the TMT is not language dependent, making it one of the three, highly recommended tests by the ICCTF [32].

#### Controlled Oral Word Association Test (COWAT)

The COWAT is a test that measures semantic and phonological verbal fluency and is a recognized and sensitive indicator of cognitive functioning. It aims to say as many words as possible during 1 minute in three trials. The higher number of said words indicates better verbal fluency. The internal consistency of the test is adequate (*α* = .86) [35, 36]. This is the third test recommended by the ICCTF for the assessment of cognitive impairments [32].

#### Hospital Anxiety and Depression Scale (HADS)

The HADS uses a 14-item scale with 7 items per subscale: HADA (Anxiety) and HADD (Depression). Items are scored from 0 to 3 with a total score for each scale of 0 to 21. The higher the score, the more pronounced the symptoms. The cut-off point for possible cases is more than 8 points [37]. The Spanish version of this scale has been validated in an oncological sample and shown an internal consistency of α = .85 for HADA and α = .87 for HADD [38].

#### EORTC QLQ C-30 (version 3) and BR23 breast cancer module

This instrument was developed to assess quality of life in cancer patients using 30 questions about the quality of life experienced by the patient during the past week. The first 28 items include questions about different symptoms and are answered on a scale of 1 (*not at all*) to 4 (*very much*), while the last two items ask patients to rate their self-perceived overall health and overall quality of life on a scale of 1 (*very poor*) to 7 (*excellent*). The items are grouped into functional scales (physical, role, emotional, cognitive, social, and global) and a symptom scale (fatigue, nausea and vomiting, dyspnea, sleep problems, loss of appetite, constipation, diarrhea, and financial impact). This instrument was developed to be administered to cancer patients and is widely used in studies with these patients. The Spanish version of the test has shown good psychometric properties (*α* > .70) [39]. The BR23 module adds 23 items rated from 1 (*not at all*) to 4 (*very much*) and it was developed to assess specific features in breast cancer patients using five, multi-item scales: body image, sexual functioning, systemic therapy side effects, breast symptoms, and arm symptoms. Additionally, single items assess sexual enjoyment, future perspectives, and being upset by hair loss. In EORTC QLQ C-30 (version 3) and BR23 breast cancer module, higher scores reflect a lower QoL in the different features assessed [40].

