#### Secondary outcomes

The secondary outcomes include changes in the level of QoL, anxiety, and depressive symptoms (QLQ C-30, BR23, and HADS) of the participants in both intervention groups, with better scores for the UP intervention group. Therefore, changes are expected in T1 with respect to T0 in the mean for QLQ C-30, BR23, and HADS scores and are expected to persist in T2. These scores are expected to remain stable in the waitlist group. The expected changes are manifested by a decrease in the score for each scale. Zwerenz et al. [24] used the HAD scale, specifically the depression subscale (HADD), to measure depressive symptoms and considered a variation of at least two points in the different measures as a clinically significant change in symptoms. Therefore, this study assumes that a variation of at least two points from the mean on the anxiety (HADA) and depression (HADD) subtests indicates a clinically significant change in symptom intensity. According to various authors, a change in QLQ C-30 scores of 5 to 10 can be considered as “little” change in terms of quality of life and of 10 to 20 as “moderate” change, while if this variation is greater than 20, the change is “very much” and a change of 10 points is considered meaningful [25, 26]. Thus, this study considers that a variation of 5–10 points, 10–20 points, and more than 20 points from the mean are considered as slight, moderate, and high significant changes, respectively.

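### The stated scoring direction for the QLQ-C30 contradicts the anchors of its two global items, so a gain in global quality of life would be read as a loss

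*Protocol article*

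**What the plan says.** In the section on the EORTC QLQ C-30 and BR23, the article explains that "the last two items ask patients to rate their self-perceived overall health and overall quality of life", and gives the response range as "overall quality of life on a scale of 1 (*very poor*) to 7 (*excellent"). It places the global scale with the functional scales, apart from the symptom scale: "The items are grouped into functional scales (physical, role, emotional, cognitive, social, and global"). The section then closes with one direction for both questionnaires, without exception: "higher scores reflect a lower QoL in the different features assessed".

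Outcomes {12}, Secondary outcomes, repeats that direction when it describes the benefit expected on QLQ-C30, BR23 and HADS: "The expected changes are manifested by a decrease in the score for each scale". The same section sets change bands for the QLQ-C30 of 5-10 points (slight), 10-20 points (moderate) and more than 20 points (high), with no sign attached.

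**The concern.** The two descriptions of the global items cannot both hold. If 7 is the best rating, a higher score cannot mean lower quality of life, and a decrease cannot be the expected benefit. This is not detail that an article leaves to an analysis plan. The direction is stated, stated twice, and wrong for this scale on the article's own anchors. An analysis plan that scored the global items as they are answered would contradict the published protocol.

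What is at stake is the reading of one secondary outcome. Quality of life is also named in the primary objective (Background and rationale {6a}), in both hypotheses (Objectives {7}), and in the comparisons that Statistical methods {20a} treats as most important. A sign error on the global scale would therefore be visible in the trial's conclusions.

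**Working it through.** The article gives no figure to reproduce on this point. The check is one of direction, followed by an illustration of size.

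**1. Direction, from the article's own descriptions**

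| Scale | How it is answered or scored | Better is | Does 'decrease = benefit' fit? |
|---|---|---|---|
| HADS anxiety, depression | higher means more pronounced symptoms | lower | yes |
| QLQ-C30 symptom scales (items 1-28) | 1 not at all, 4 very much | lower | yes |
| Other QLQ-C30 functional scales (items 1-28) | same raw anchors; direction after any transformation not stated | depends on scoring | on raw items, it may |
| QLQ-C30 global (last two items) | 1 very poor, 7 excellent | higher | no |
| BR23 sexual functioning, sexual enjoyment | 1 not at all, 4 very much; item wording not shown | not determined | uncertain |

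Only the global row is a demonstrated contradiction. The article mentions reverse-scored items for the FACT-Cog but says nothing of the kind for the QLQ-C30 or BR23, so no stated reversal resolves it.

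**2. Size, for illustration**

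Assume the mean of the two global items is rescaled linearly to 0-100: score = (raw − 1)/6 × 100. The article does not state this scale.

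- Mean rating from 4 to 5: 50.0 to 66.7, a change of +16.7.
- Mean rating from 4 to 6: 50.0 to 83.3, a change of +33.3.
- Mean rating from 6 to 4: 83.3 to 50.0, a change of −33.3.

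By the anchors, the first two are improvements and the third is a deterioration. Under the stated direction, the first two are worsening and the third is benefit. In absolute size, 16.7 lies in the moderate band (10-20) and 33.3 in the high band (above 20). The reversal of sign does not depend on the rescaling; only the point values do.

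**3. What the bands imply about the score**

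A single global item, or the mean of the two, can change by at most 7 − 1 = 6 raw points, which lies inside the 5-10 band. The sum of the two can change by at most 2 × 6 = 12, inside the 10-20 band. The band above 20 cannot be reached on raw global scores. A rescaled score is therefore the plausible intention, but the bands are not strictly inapplicable to raw scores.

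**4. Effect on the analysis**

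Statistical methods {20a} plans mixed linear models and a bias-corrected Cohen's d. Reversing a scale multiplies each estimate by −1 and leaves its absolute size and standard error unchanged. A two-sided p-value is also unchanged; the article does not state sidedness. What goes wrong is the label of benefit or harm.

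**5. A separate clerical slip**

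The MFE-30 is called a 5-point scale answered from 1 to 4, and "The minimum score is 30 and the maximum score is 120". Four categories give 30 × 1 = 30 and 30 × 4 = 120, so the anchors and the range agree. Five categories starting at 1 would give a maximum of 30 × 5 = 150. Only the word for the number of points is out of line.

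**The case against.** The strongest reply is that these sentences describe expectations and are not a decision rule. The bands are unsigned, the models do not use the stated direction, and an analyst who looks at the questionnaire will see which way the global items run. An unstated reversal may already be intended, and the outcome is secondary.

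Much of this stands. Harm requires that the sentences be applied literally, the estimates themselves are safe, and neither the sample size nor the cognitive primary outcomes are touched. It does not remove the contradiction: the expected benefit for global quality of life is written as a decrease, and no reversal is recorded to make that true.

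A reader might infer more than the article supports:

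- **That the BR23 direction is also shown to be wrong.** It is not. The poor-to-excellent anchors belong only to the two global items. BR23 items run from not at all to very much, which fixes no direction without the item wording. For sexual functioning and enjoyment there is a reasonable doubt, no more.
- **That scales of opposite direction would cancel in a combined score.** No summary mixing scales is planned.
- **That the bands cannot be applied to raw scores at all.** Step 3 shows this is too strong, and details of transformation may sit in a fuller document.
- **That the MFE-30 slip puts a primary measure in doubt.** The anchors and range agree with each other, so it is a wording error.

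**Conclusion.** The article is wrong as written on one scale. For QLQ-C30 global health and quality of life, the stated meaning of a higher score and the stated direction of benefit both contradict the stated anchors. Taken literally, they reverse the interpretation of that outcome: a one-point gain in mean rating would be reported as 16.7 points of worsening and a two-point gain as 33.3, if scores are rescaled to 0-100. This rests on the anchors as printed and on there being no reversal outside the article.

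It should be corrected, but it does not threaten the primary analysis, the sample size or the size of any estimated effect. It would be tempting to say that the trial will report quality of life backwards. The article supports only that its written rule would do so for the global scale if followed.

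**What to change.** - In the EORTC section and in Secondary outcomes, limit the statements that a higher score is worse and that benefit is a decrease to the symptom scales and HADS.
- State that benefit on global health and quality of life, and on any other scale scored so that higher is better, is an increase. A short table giving the direction for each scale would settle the remaining functional scales too.
- State the score scale actually used, and apply the 5, 10 and 20-point bands on it in each scale's beneficial direction.
- Check the direction of the BR23 sexual functioning and enjoyment scores against the item wording and enter it in the table.
- As a clerical correction, make the MFE-30 description say four response options, once the form in use is confirmed.

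The cost is a few sentences or one table in the protocol or analysis plan, ideally before outcome data are analysed. No data collection, model or sample size changes.

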#### .Demographic Variables Questionnaire

This questionnaire was prepared by the researchers of this work to collect some sociodemographic and clinical variables that are intended to be analyzed such as age, sex, marital status, level of education, psychiatric medication (if any), type of cancer and cancer stage, kind of cancer treatment, time from cancer diagnosis to end of chemotherapy, and fibromyalgia diagnosis.

### Plans to promote participant retention and complete follow-up {18b}

In order to minimize loss to follow-up, once the intervention period is finished, participants who complete the intervention sessions will receive phone calls to remind them of their participation in the study and to set up the follow-up evaluation session.

### Data management {19}

The members of the research team in charge of collecting the data will receive prior training on the correct way to fill out the questionnaires, in order to unify criteria and resolve possible doubts before starting the evaluation. To ensure the accuracy of the data entry, it will be carried out independently by two researchers. If any discrepancies appear, they will be resolved by going back to the data source. Finally, the trial steering committee, consisting of the principal investigator and members of the research team, will be responsible for monitoring the quality and accuracy of the data.

To ensure participants’ anonymity, once they are included in the study, their information will be treated using a code number. Data obtained from the questionnaires and all sociodemographic and clinical data will be collected in paper format and stored in a locked filing cabinet during and after the trial. The researchers shall retain all data collected for up to 5 years after the end of the study.

### Confidentiality {27}

Participants must complete an MMSE screening test before entering the study. If the scores of the screening test indicate cognitive deterioration, the participant will be provided an informed consent with information about the trial, the confidentiality of the results, the possibility of withdrawing from the study at any time and without giving any reason, and no negative consequences in the event of withdrawal. All informed consent forms will be kept in a locked cabinet at the Reina Sofía University Hospital. The participants’ information will be encoded with a unique ID to ensure confidentiality and stored in a locked file at the hospital. The research team will only have access to the clean dataset with the encoded participant information. These datasets will be protected by a password and stored in a computer that will only be accessible to the members of the research team.

### Plans for collection, laboratory evaluation, and storage of biological specimens for genetic or molecular analysis in this trial/future use {33}

The data collected will be used only for the purposes of this research and no biological samples will be collected.

## Statistical methods

### Statistical methods for primary and secondary outcomes {20a}

The obtained data will be analyzed following the intention-to-treat (all randomized patients are included in the analysis) and per protocol (only patients with post-treatment assessment are included in the analyses) approaches. In an intention-to-treat analysis, incomplete or missing data will be considered using the maximum likelihood estimation method. First, ANOVA or chi-square tests will be performed to compare the demographic variables and outcome measures at baseline (T0). Second, to examine longitudinal changes over time (baseline, post-treatment, and follow-up) and between-group differences in the mentioned variables, mixed linear models will be used, since these models are more precise than repeated measures ANOVA [41]. The Friedman test will be performed to analyze a potential group-level effect among participants receiving the intervention together. In addition, Cohen’s *d* with bias corrections will be calculated to determine the effect size of the between-group comparisons. The most important analysis will be performed between the two active groups (the neuropsychological treatment group and the transdiagnostic treatment group) and the control group, as well as a comparison between both active groups to observe the evolution of cognitive deficits, anxiety-depressive symptoms, and quality of life of the participants just after the application of the interventions and at 6 months of follow-up. Once the analyses are performed, summary tables will be provided for all the planned evaluations: baseline (T0), end of treatment (T1), and follow-up at 6 months (T2). The results will be presented in the form of frequency tables and by means of descriptive statistics (the mean, standard deviation, and percentages) to summarize the characteristics of both the total sample and the participants in each of the three groups. Finally, the results of the study will be reported in accordance with the 2010 statement of the Consolidated Standards of Reporting Trials (CONSORT) [42] and the 2013 guidelines for Standard Protocol Items: Recommendations for Interventional Trials (SPIRIT) [43].

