**Methods:**

A three-arm, randomized superiority clinical trial with a pre-post and repeated follow-up measures intergroup design using a 1:1:1 allocation ratio will be performed. One hundred and twenty-three cancer survivors with mild to moderate cognitive impairment will be randomly assigned to one of the study interventions: a cognitive rehabilitation intervention group, an intervention group with UP intervention, or a control group on the waiting list. The primary outcome is to observe a significant improvement in cognitive function in both intervention groups and a significant decrease in emotional impairments in comparison with the waitlist group. Improvements in anxiety, depression, and quality of life are also expected as secondary outcomes. These results will be maintained at 6 months of follow-up.

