### Intervention description {11a}

Unified Protocol for the Transdiagnostic Treatment of Emotional Disorders (UP). The UP intervention will focus on a deficit in emotional regulation common to all emotional disorders (ED). Specifically, the intervention will address the adaptive value of emotions and promote tolerance to intense emotions as well as identify and modify dysfunctional emotional regulation strategies. Patients will receive 8 group therapy sessions (8–10 cancer survivors per group) with all UP modules [20]. The Spanish version of the therapist’s guide and the patient’s workbook will be used [21]. All patients will receive the workbook to inform them of the contents of each session, aid them in doing the recommended exercises between sessions, and help them once the treatment is completed. The treatment will last 8 weeks (one session per week) as follows:*Session 1: Motivation for change and commitment to treatment.* The main objectives of the first session are to establish the therapeutic relationship and promote motivation for change. Therefore, tasks pursuing that goal will be carried out such as the analysis of the advantages and disadvantages of change and the setting of treatment goals or life goals.*Session 2*: *Understanding emotions.* The second session will focus on teaching the adaptive components of emotions in patients and will begin by working with the concept of emotion-driven behaviors (EDBs), differentiating between three emotional components: behaviors, thoughts, and physical reactions.*Session 3: Emotional awareness training. Learning how to observe experiences.* In this session, patients will be trained in emotional awareness through the practice of exercises focusing on the present without judging what they are perceiving. For example, exercises involving mood induction with music.*Session 4: Cognitive restructuring.* The objective of this session is to promote cognitive flexibility. To achieve this aim, participants will be trained to identify and modify non-adaptive thoughts (e.g., through cognitive restructuring or positive self-instruction).*Session 5: Emotional avoidance and EDBs.* This session will analyze emotional avoidance patterns and EDBs as well as their role in the development and maintenance of emotional disorders. In addition, patients will be trained to modify their dysfunctional behaviors.*Session 6: Physical sensations tolerance.* In this session, the objective is to train patients in improving their tolerance to physical sensations. To this end, participants will learn to identify uncomfortable inner physical sensations associated with emotions using breathing exercises.*Session 7: Situational and interoceptive emotional exposure.* The objective of this session is to expose the patient to emotions by promoting habituation instead of emotional avoidance. A situational and emotional avoidance hierarchy will be developed and followed by exposure exercises for that purpose.*Session 8: Maintenance of treatment gains and relapse prevention.* In the last session, participants will check their progress and what was learned in previous sessions will be recapitulated to promote the later use of this knowledge once the intervention is over. The aim is to provide patients skills to deal with demanding situations in the future.

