The intervention will be carried out in groups with a maximum of 5 participants per group [17] and consists of 8 weekly sessions of 2 h each: the first hour for memory training and the second for processing speed exercises (PSE). Contents for 8 weeks:*Session 1: Clustering strategies and PSE.* In the first session, the goal is to learn how to organize a list of verbal or visual stimuli into meaningful categories and clustering during the first hour. To achieve this goal, the psychologist will introduce the session and explain the strategies and exercises to practice them. In the second hour of the session, the participants will be trained in processing speed using the InSight program. The psychologist will remain in the room to answer any questions and support the participants while they do the computerized exercises.*Session 2*: *Summarizing strategies and PSE.* In the first hour of this session, participants will be trained to organize, summarize, and select the main ideas and details in order to remember text-based information. Once the strategies have been explained, paper-based exercises will be used. Later, patients will do processing speed exercises on computers under the psychologist’s supervision.*Session 3*: *Visualizing strategies and PSE.* The first hour of the third session focuses on teaching visualizing strategies to remember different items. In the same line as previous sessions, the strategy will be explained first and the practical exercises will be performed later. The second hour will focus on processing speed exercises using the Posit Science InSight program as well.*Session 4*: *Association strategies and PSE.* In the first hour of this session, the objective is to use association to remember items. In this case, the strategies will be taught using both visual and verbal materials. In the second hour, participants will be trained in processing speed as usual with the psychologist’s support when necessary.*Sessions 5, 6, 7, and 8: Revising strategies and PSE.* In the last four sessions, what was learned in the previous sessions will be entrenched with additional practice exercises in the first hour. Thus, mixed exercises will be done in these sessions where participants are asked to apply different strategies to each exercise and solve doubts. Likewise, processing speed training with the Insight program will be provided in the second hour.

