Control group on waiting list. Once the interventions in groups 1 and 2 have been completed, the control group will receive the neuropsychological treatment described above. The group on the waiting list will participate in all the evaluations (T0, T1, and T2)

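### The Friedman test named for the therapy-group effect cannot assess clustering; unless the mixed model carries a post-baseline therapy-group effect, standard errors involving the active arms are too small whenever the ICC is above 0

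*Protocol article*

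**What the plan says.** All references are to the protocol article.

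- Intervention description {11a}, UP: "Patients will receive 8 group therapy sessions (8–10 cancer survivors per group) with all UP modules".
- Intervention description {11a}, neuropsychological treatment: "The intervention will be carried out in groups with a maximum of 5 participants per group".
- Intervention description {11a}, waitlist: "Once the interventions in groups 1 and 2 have been completed, the control group will receive the neuropsychological treatment described above". The same paragraph has the waitlist assessed at T0, T1 and T2. Trial design {8} describes the later treatment as an option.
- Statistical methods {20a}, main model: for change over time and "between-group differences in the mentioned variables, mixed linear models will be used, since these models are more precise than repeated measures ANOVA". No random-effects structure is given.
- Statistical methods {20a}, therapy-group effect: "The Friedman test will be performed to analyze a potential group-level effect among participants receiving the intervention together". This is the only provision for clustering, and the article does not say what would follow from the result.
- Sample size {14}: 108 evaluable participants, 36 per arm, raised to 123 (41 per arm) for 13% withdrawal. No design effect is mentioned.

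**The concern.** The plan recognises that people treated together may come to share outcomes, and then names a method that does not address this. The Friedman test is a rank test for related measurements in complete blocks, whereas therapy groups consist of different people. It returns no variance component and no ICC, and it leaves the standard errors of the mixed model as they were.

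Two things are at stake. First, both active arms are expected to improve from T0 to T1, so a significant Friedman result could be misread as a therapy-group effect, and a non-significant one as reassurance. Second, if nothing else in the analysis carries the clustering, intervals are too narrow and type I error exceeds its nominal level. The clustering is unequal. It is strongest in UP, the arm of the primary objective, and it lies on both sides of the UP versus neuropsychological comparison, which is the first hypothesis.

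**Working it through.** **1. The plan's own figure.** Using the repeated-measures between-factors form with f = 0.25, three measurements, correlation 0.5, three arms and alpha 0.05, the noncentrality is f²·N·m/(1+(m−1)ρ) = 0.0625 × 108 × 3/(1 + 2 × 0.5) = 10.125. Power is 0.809, so 108 is reproduced exactly with participants treated as independent. For withdrawal, 108 × 1.13 = 122.04, rounded up to 123.

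**2. Numbers of therapy groups.** For UP, 41/9 = 4.6, or 36/9 = 4, so about 4–5 groups. For neuropsychological treatment, 41/5 = 8.2, so at least 9 groups. The waitlist is ungrouped at T1.

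**3. What the Friedman test responds to.** This was simulated with 36 participants in 4 therapy groups of 9, three time points and 3,000 replicates, testing at 5%.

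| Layout | Situation | Rejection |
|---|---|---|
| Participants as blocks, times as conditions | No time effect; stable group effect with ICC 0 / 0.10 / 0.30 | 6.1% / 5.1% / 5.6% |
| Same | 0.5 SD change after T0, ICC 0 | 74% |
| Same | Group effect starting after T0, ICC 0.10, no mean change | about 12% |
| Times as blocks, therapy-group means as conditions | ICC 0 | about 16% |
| Same | ICC 0.10 | about 38% |

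The usual layout does not see a stable group effect and reacts strongly to time. The 12% arises only as an apparent time effect. The last layout reacts to clustering but is invalid: it rejects 16% of the time with no clustering, because its blocks are the same people measured again.

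**4. Consequence if the model has no therapy-group effect.** The design effect per arm is DE = 1 + (m − 1)·ICC, with m = 9 for UP, m = 5 for neuropsychological treatment, and DE = 1 for the waitlist at T1. With equal arms, the ratio of true to naive standard error is √((DE_A + DE_B)/2), and actual alpha is 2·P(Z > 1.96/ratio). The ICCs are assumptions.

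| ICC | DE, UP | DE, neuropsych. | UP vs waitlist: ratio, alpha | Neuropsych. vs waitlist: ratio, alpha | UP vs neuropsych.: ratio, alpha |
|---|---|---|---|---|---|
| 0.01 | 1.08 | 1.04 | 1.02, 5.5% | 1.01, 5.2% | 1.03, 5.7% |
| 0.05 | 1.40 | 1.20 | 1.10, 7.4% | 1.05, 6.2% | 1.14, 8.6% |
| 0.10 | 1.80 | 1.40 | 1.18, 9.8% | 1.10, 7.4% | 1.26, 12.1% |

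Simulation of an unadjusted t-test (36 per arm, 10,000 replicates) agrees. At ICC 0.05 it gave 7.7%, 6.8% and 8.1% for the three comparisons in that order, and at ICC 0.10 it gave 9.9%, 7.1% and 11.9%.

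**5. The waitlist at T2.** Waitlist participants who have taken up the neuropsychological treatment by then were treated in groups too. In the extreme case that all have, their DE at ICC 0.05 is 1.20. The UP versus waitlist ratio becomes √((1.40 + 1.20)/2) = 1.14 and alpha 8.6%.

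**6. Which therapy-group term works.** T0 precedes randomisation, so therapy groups do not yet exist. Take 36 per arm, unit variance, correlation 0.5, and UP versus waitlist on change from T0 to T1. The variance of a change is 2(1 − 0.5) = 1.

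- No group term: SE = √(1/36 + 1/36) = 0.236.
- Group intercept constant over time: it cancels from the change, so SE is still 0.236.
- Clustering that starts after baseline (ICC 0.05, total variance held at 1): SE = √(1.40/36 + 1/36) = 0.258.

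The ratio 0.258/0.236 is the 1.10 of step 4. Only a term that acts after baseline recovers it.

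**The case against.** The strongest objection is that a reader might infer from this that the mixed model treats participants as independent and that its standard errors are therefore too small. The documents do not support that stronger reading, for three reasons.

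- The article gives no random-effects structure. Such terms are commonly left to an analysis plan, which is not shown, so silence here is no error. Independence is a plausible inference, since the Friedman test is the only clustering provision and 108 is reproduced without a design effect, but it remains an inference.
- It does not follow from the failure of the Friedman test. Even a valid test of clustering would leave the model's standard errors unchanged; what matters is whether the model contains a therapy-group effect.
- Standard errors are understated only if the ICC is above 0. At 0.01 the effect on type I error is slight.

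All of this stands, and it makes the second half of the point conditional. It does not rescue the sentence on the Friedman test. That is a method the article states, for a purpose the method cannot serve, and added detail elsewhere would not make it right.

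Two further cautions also stand. Treating the waitlist as unclustered is safe only at T1. And with about 4–5 UP groups, separate group variances per arm would be poorly estimated, so they should not be required.

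**Conclusion.** The protocol article names the wrong tool for the therapy-group effect. This holds without any assumption about the ICC.

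The consequence for inference is conditional on two things: an ICC above 0, and a mixed model without a post-baseline therapy-group effect. Under both, at assumed ICCs from 0.01 to 0.10, type I error at a nominal 5% runs from about 5.5% to 9.8% for UP versus waitlist and from 5.7% to 12.1% for UP versus neuropsychological treatment. These figures take UP groups of 9, neuropsychological groups of 5, equal arms and an ungrouped waitlist at T1. They come from a large-sample formula that the simulation supports. Whether the trial's model will in fact omit the term cannot be read from the article.

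**What to change.** 1. Delete the Friedman test from Statistical methods {20a}.
2. Record each participant's therapy-group number during delivery. Without it, no later analysis can account for clustering.
3. Specify a partially nested linear mixed model with participant-level repeated measures and a therapy-group random effect that acts on post-baseline outcomes only. Either use T0 as a covariate, or use a group-by-time random effect. A group intercept constant over time is not enough.
4. Treat waitlist participants as ungrouped at T1. At T2, assign those who took up the neuropsychological treatment to the therapy group in which they received it.
5. Use Satterthwaite or Kenward-Roger degrees of freedom, and report the ICC. Arm-specific group variances are optional.

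The cost is a change of analysis wording and one identifier variable. The downside is fewer degrees of freedom and wider intervals, mainly for UP because of its few groups.
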